
**Fig. 2 Fig2:**
[figure not shown]
Flowchart of measures and timeline of our multi-site, single-blinded, randomized controlled trial *Note*. Each site will be comprised of a sample of 20 middle-aged adults and 20 older adults with normal hearing (NH), as well as 20 older adults with age-related hearing loss who use hearing aids. An equal number of males and females will be recruited into each training group within each of the age/hearing groups. Both the executive function training group and wait-list control group will participate in Pre- and Post-Training assessments. During the 12-week intervention phase, the executive function training group will complete an at-home cognitive training program three times a week (30 minutes/session). The wait-list control group will not complete any form of cognitive training during the duration of the experiment, but will be offered the materials at the end of the study

### Randomization

Upon completion of the screening and baseline assessments, participants will be randomized to either the executive function training or wait-list control group. Randomization of participants will be completed within each of the three groups (i.e., middle-aged, older adults, hearing aid users) using a computerized random number generator. Final cohorts will be semi-randomized in order to attain an equal number of participants in the training and control groups and to balance the number of males and females within each age/hearing group.

### Blinding

Participants will be made aware of the two groups in which they could be randomized to and will know which of the two groups they have been assigned to following the baseline assessments. Efforts will be made so that the evaluators conducting the Pre- and Post-Training assessments will be blind to the participants’ randomization status. For example, the research personnel responsible for calling participants during the 12-week period will be different than the research personnel completing the post-training evaluations.

### At-home executive function training group

After the Pre-Training phase, participants randomized to the executive function training group will complete an at-home computerized cognitive training program three times a week for a total of 12 weeks (each session lasting 30 min). The training protocol will involve a custom-written program that has been used in previous research studies assessing cognitive and gait outcomes, but was previously administered in a controlled laboratory environment [39–41, 43]. Specifically, the training is comprised of three distinct modules (Stroop, dual-task, *n*-back), which aim to improve different aspects of executive functioning such as inhibition and task switching-abilities, divided attention, and working memory, respectively. Participants will be encouraged to evenly disperse the training throughout the week (i.e., 48 h between sessions). However, participants have the flexibility to complete the sessions according to their own schedule. Each training session (30 min) is comprised of two different modules (each 15 min). Participants may take a break between modules, but not during a module. The computerized program can be completed on either a laptop, desktop, or tablet, but should be held consistent throughout the 12-week duration of the training. Participants will also be instructed to work as fast as they can without making any mistakes, as both reaction time (milliseconds) and accuracy will be recorded for all three tasks. After each session, a performance feedback graph will be presented to provide encouragement and allow participants to track their progress.

The Stroop module aims to improve inhibition and task-switching using four separate conditions (familiarization, reading, inhibition, and switching) presented at different points throughout the training period. Participants will be required to press the appropriate letter key on their keyboard or press the appropriate button on their tablet, based on the condition presented. In the familiarization condition, a single letter will be presented on the screen. In the reading condition, asterisks will form a letter on the screen. In the inhibition condition, smaller letters will make up a larger letter (e.g., copies of small letters “L” to form a larger “H”), and participants will need to inhibit the automatic response of indicating what the smaller letter is, and instead indicate what larger letter is formed. In the switching condition, participants will need to alternate between reporting the smaller letters presented, or the larger letters that are formed, depending on the goal as indicated by whether a white frame is surrounding the group of letters or not.

The visual *n*-back module targets the updating and maintenance of information in working memory. Participants will be instructed to make a keyboard response or button press on a tablet indicating whether the letter they see is the same or different from the one presented one previously (1-back), two previously (2-back), or three previously (3-back). The more challenging 2-back and 3-back trials will make up a larger proportion of the trial type distribution as the training progresses in order to enhance the difficulty level. Of note, the modality of the *n*-back in the cognitive training differs from the modality used in the dual-task experiment (i.e., visual during training versus auditory during the dual-task experiment).

The dual-task module aims to improve divided attention. Participants will complete a visual discrimination task whereby they will need to make a response to one type of image (single-task; i.e., modes of transportation or fruits;) or two types of images concurrently (dual-task; i.e., one image reflecting a mode of transportation and another image of a fruit). Participants will complete pure blocks of only single-task trials (single-pure trials) or only dual-task trials (dual-pure trials) or will complete mixed blocks that randomly involve one (single-mixed trials) or both tasks (dual-mixed trials). For the dual-task trials, participants will be instructed to respond to both stimuli equally. However, as the training progresses, participants will need to prioritize one hand over the other to increase the level of difficulty (i.e., in the dual-task trials when two images are presented, participants will be asked to make a response using their left or right hand first before making a response with the other hand).

### Waitlist control group

Participants randomized to the wait-list control group will complete both the Pre- and Post-Training assessments but will not partake in any form of cognitive training during the 12-week period. Weekly phone calls will ensure that participants are maintaining a consistent lifestyle and that they are not starting any other cognitive training programs. The weekly phone calls will also allow for a similar level of social interaction amongst the research personnel and the participants across the wait-list control and training groups in order to control for this possible confound. Upon completing the study, the wait-list control group will be offered the materials for the at-home executive function training program, and researchers will be available to offer assistance if needed.

### Data analysis

#### Planned analyses

All data analyses will be completed using IBM SPSS Statistical Software and/or R. Data will be screened and corrected for normality, outliers, and missing values. Descriptive statistics (e.g., means and standard deviations for continuous variables; frequencies and percentages for categorical variables) will be presented for the demographic and baseline characteristics. Chi square tests (for categorical variables) or One-Way ANOVAs (for continuous variables) will be used to determine if there are any differences between groups at baseline (i.e., middle-aged vs. older adults vs hearing aid users; training vs. control groups).

In order to evaluate our primary hypothesis (i.e., that executive function training will lead to greater improvements in dual-task performance compared to a wait-list control group), separate 3 × 2 × 2 Mixed Factorial ANOVAs will be conducted for each of the primary outcome measures (i.e., 2-back accuracy and reaction times, CRM accuracy, temporal gait parameters, posturography variables, DTC scores), whereby the Between-Subjects factors will include Age/Hearing Group (middle-aged, older adult, hearing aid users) and Training Group (cognitive training, control), the Within-Subject factor will include Time (pre- vs. post-evaluations), and Covariates will include sex and education. Observation of a statistically significant Time by Training Group interaction in any of the primary outcome measures will be considered preliminary evidence for training efficacy. In order to examine our second and third hypotheses (i.e., that largest improvements in dual-task performance and greatest augmentation of brain activity will be found in older hearing aid users, followed by normally-hearing older adults, and then middle-aged adults) separate One-Way ANOVAs will be used on the dual-task and HbO change scores within the cognitive training group, whereby the Between Subjects factor will include Age/Hearing Group (middle-aged, older adult, hearing aid users). Observation of a statistically significant main effect of Group will be followed up by post hoc pairwise analyses with Bonferroni corrections in order to determine whether our hypotheses are supported.

Linear mixed effects models will also be fitted for each of our outcome measures, particularly if there is a large amount of missing data or if there is an unequal amount of variance across groups. Specifically, Fixed effects will include Age/Hearing Group (middle-aged, older adult, hearing aid users), Training Group (executive function training, control), Sex (male/female), and Time (Pre- vs. Post-Training), Random effects will include the individual participants, and Covariates will include education.

Lastly, in order to elucidate whether brain activity reflects neural compensation or inefficiency, correlations between dual-task performance and HbO levels will be conducted at baseline and after 12 weeks. All statistical tests will be two-tailed, and a *p*-value of less than 0.05 will be considered to indicate statistical significance. Effect sizes will be calculated using Hedges’ *g.*

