## Methods/design

### Design

We will conduct a multi-site, single-blinded, randomized controlled trial involving at-home executive function training over a 12-week period. A total sample of 60 participants will be recruited at each testing site, comprised of 20 middle-aged adults (aged 45–60 years old) with normal hearing, 20 older-adults (aged 65–80 years old) with normal hearing, and 20 older-adults (aged 65–80 years old) with hearing impairment who use hearing aids (with a minimum of 6 months of experience using hearing aids). Participants will be randomized to either an executive function training group or a wait-list control group. The executive function training group will complete the home-based computerized cognitive training program during a 12-week period, while the wait-list control group will not complete any form of cognitive training during the 12 weeks. Participants in the wait-list control group will be offered the cognitive training program at the end of the study. Before and after the 12 week-period, participants in both groups will be asked to complete a series of cognitive, sensory, and mobility tests during two separate in-person sessions.

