### Sample size

Sample size calculation is based upon prior intervention studies that utilized the same cognitive training protocol and that reported pre- and post-training changes in our primary outcome measures (e.g., gait or postural variables, auditory working memory) for healthy older adults. Specifically, Pothier et al. [58] used the same executive function training as the current study combined with placebo stretching as one of four training groups and reported a significant Time (pre- vs. post-training) by Training Group interaction (total *n* = 90, *d* = 0.304, actual power = 0.96). For the group receiving the same cognitive training as the current study, a moderate effect of Time on gait speed was found (*n* = 23, *d* = 0.478), with an average increase of 0.13 m/s following training. Additionally, Bruce et al. [46] used a similar cognitive training protocol as the current study in combination with recumbent bicycling (delivered either sequentially or simultaneously), where a significant main effect of Training Group (sequential vs. simultaneous training format) was found for auditory *n*-back accuracy (*n* = 42, *d* = 0.718, actual power = 0.95). The effect size for auditory *n*-back improvement was large, whereas the effect size for gains in mobility was small to moderate. This is consistent with results from Downey et al. [40] where the same cognitive training protocol as the current study was utilized, demonstrating a large effect size for improvements in* n*-back dual-task costs (*g* = -0.83), but a small effect size for gains in walking speed dual-task costs (g =  − 0.11). The recommended (G*Power) sample size to achieve a power of 0.95 at an alpha level of 0.05 for the Training Group x Time interaction for walking speed is 18 per group. Therefore, we aim to recruit 20 participants in each of the three groups (normal-hearing middle-aged adult, normal-hearing older adults, older hearing aid users) to allow for 10% attrition and a balanced design.

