### Auditory 2-back paradigm

*2-Back Task:* The same auditory 2-back task as the Concordia site [41] will be used; however, trials will last 60 s instead of 30 s in order to capture a sufficient amount of reliable posturography data [25]. The amplitude of the loudspeakers will be individually adjusted using an auditory 1-back task to ensure optimal audibility and comfort across participants. Specifically, participants will hear 15 untimed, single digits where they will have to repeat the digit they heard out loud to the researcher immediately after the digit is presented. In order to participate in the study, participants must attain at least 70% accuracy or higher. If the amplitude is uncomfortably loud, it will be reduced (ensuring at least 70% accuracy) and the amplitude will then be set at this level for the remainder of the experiment. Accuracy and reaction time will be measured using a handheld gaming controller (Forty4 Wireless Gaming Controller). During the main experimental task, participants will make a button press indicating whether the number they are currently hearing is the same or different than the number presented *n* steps previously (i.e., 1-step previously during the practice trials, or 2-steps previously for the 2-back task). During single-task conditions, the participants will complete the 2-back while sitting on a chair on top of the force plate within StreetLab at the same approximate eye height as standing.

*Postural Task.* Static balance will be measured by having participants stand with their feet shoulder-width apart on a force platform. In order to control for differences in hand positions across the single-task standing and dual-task trials (since participants use handheld joysticks during the 2-back task), participants will be required to hold the joystick in the same position as the dual-task trials (but will not need to make any button responses). In order to manipulate postural load, participants will complete the standing balance task with their eyes open and eyes closed. Postural measures will include spatial (centre of pressure path length; cm), temporal (velocity; cm/s) and variability (root means square, standard deviation) measures in the anterior–posterior (front and back) and medial–lateral (side-to-side) orientations.

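### The 2-back outcomes and shared secondary tests are measured at both sites, but the plan does not say whether they are pooled or tested by site, and neither stated model has a Site term

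*Protocol article*

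**What the plan says.** Under Design, "A total sample of 60 participants will be recruited at each testing site", split equally over three age/hearing groups, so two sites give 120 people. The auditory 2-back (accuracy, reaction time and dual-task cost) is a primary outcome in both the PERFORM (Concordia) and StreetLab (KITE) protocols. Gait is measured only at Concordia. Posturography and the CRM task are measured only at KITE. The neuropsychological, sensory, Mini-BESTest and questionnaire measures are common to both sites.

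The StreetLab section presents its 2-back as the Concordia task with changes, for example that "trials will last 60 s instead of 30 s in order to capture a sufficient amount of reliable posturography data". The single-task 2-back is done standing at Concordia and seated at KITE. Loudness is set to a level giving 100% accuracy at Concordia and at least 70% at KITE. The companion motor task is treadmill walking at one site and standing balance at the other.

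Under Planned analyses, "separate 3 × 2 × 2 Mixed Factorial ANOVAs will be conducted for each of the primary outcome measures". The between-subject factors are Age/Hearing Group and Training Group, the within-subject factor is Time, and the covariates are sex and education. The mixed model for all outcome measures uses the same factors plus sex, and "Random effects will include the individual participants, and Covariates will include education". A significant Time by Training Group interaction in any primary outcome counts as preliminary evidence of efficacy. "All statistical tests will be two-tailed", and a p-value "value of less than 0.05 will be considered to indicate statistical significance". The article does not say whether a shared outcome is analysed once or once per site.

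**The concern.** The Planned analyses text can be read in two ways for the shared outcomes, and the readings can lead to different conclusions. Read on its own, one ANOVA per outcome means a single 2-back analysis of 120 people with no term for site. Read with the per-site samples, it means two separate analyses of 60. Because any significant primary outcome counts, each of those two could then be taken as a success.

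The choice concerns the only primary outcomes that the two sites have in common. While it is open, it can be made after the results are known. Each reading also has its own weakness: two verdicts on one hypothesis under the first, and an error term carrying avoidable site variation under the second.

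**Working it through.** **The plan's own figure.** The Sample size section asks for a "sample size to achieve a power of 0.95 at an alpha level of 0.05" and states that the Training Group by Time "interaction for walking speed is 18 per group". Its attrition step is 18 / (1 − 0.10) = 20 per age/hearing group, and 3 × 20 = 60, which is one site's sample. The 18 itself cannot be reproduced without assumptions, because the effect metric and the pre-post correlation are not given. The 0.304 read as Cohen's f, with two groups and correlation 0.5, gives 19 per group. Read as d, it gives 72. Nothing below depends on the 18.

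**Inputs.** Two-sided alpha is 0.05 (Planned analyses). With 60 per site (Design) and equal arms (Randomization), the comparison is 30 v 30 per site and 60 v 60 pooled. The effects come from the Sample size section: 0.304 (a Time by Training Group interaction), 0.478 (change over time in gait speed) and 0.83 in absolute value (n-back dual-task cost). Treating them as between-arm standardised differences in change is an assumption.

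**1. False success if tested by site.** The sites have different participants, so the tests are independent: 1 − 0.95² = 0.0975 per outcome. If site 1, site 2 or the pooled result may each count, simulation with 1,000,000 draws gives 0.115.

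**2. Power per site against pooled.** With two time points, the Time by Training Group test is equivalent to comparing change scores between arms. The calculation uses the noncentral t with df = 2n − 2 and noncentrality d√(n/2). At d = 0.478 the noncentrality is 0.478 × √15 = 1.85 per site and 0.478 × √30 = 2.62 pooled.

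| d | 30 v 30 (one site) | 60 v 60 (pooled) |
|---|---|---|
| 0.304 | 0.212 | 0.379 |
| 0.478 | 0.445 | 0.738 |
| 0.83 | 0.885 | 0.995 |

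After 10% attrition (27 v 27 and 54 v 54), the figures at 0.478 are 0.407 and 0.692.

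**3. Disagreement between two site tests.** This is 2p(1 − p). At d = 0.478 it is 2 × 0.445 × 0.555 = 0.49. At d = 0.83 it is 2 × 0.885 × 0.115 = 0.20.

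**4. Pooling without Site.** A constant site difference in level is present both before and after training, so it drops out of each person's change and does not touch the Time by Training Group test. A site difference D in mean retest change (in SD of change) does not drop out. With equal sites, the change variance becomes 1 + D²/4 times as large:
- D = 0.5: 1 + 0.25/4 = 1.0625, about 6% more variance and 3% more SD. Pooled power at 0.478 falls from 0.738 to 0.712.
- D = 1: 1 + 1/4 = 1.25, 25% more variance and 12% more SD. Pooled power at 0.478 falls to 0.642.

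The documents give no value for D, so 0.5 to 1 is an assumed range. A Site x Time term removes this part of the error.

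**The case against.** The article leans towards analysis by site. The abstract speaks of separate samples, recruitment is set per site, the 20 per age/hearing group matches one site, and the two testing protocols are described separately. On that reading Site is constant within each analysis and its absence from the models is no error. This stands, and it means that the missing term does harm only if the data are pooled. It does not settle the question, because the analysis section never says by site, and the per-site reading is the one that produces two tests.

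A reader might infer that testing by site falls short of the planned size. The documents do not support that: 60 per site is the plan, and 120 is only the sum of the two sites. The power comparison shows what pooling would gain. That gain also depends on the effect. At 0.83, the only cited figure for n-back dual-task cost, 89% per site is already good.

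A reader might also infer that pooling mixes two unlike tasks. The protocol presents the 2-back as the same task, and that is fair for accuracy and reaction time, despite the differences in trial length, posture and calibration. It is not fair for the dual-task cost, where the companion task is walking at one site and standing at the other. Separate reporting of that outcome is defensible.

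Nor do the documents show bias in the arm contrast. Bias would need arms unbalanced by site. Randomization equalises arms within age/hearing groups and the Figure 2 note describes equal numbers, although no site stratum is stated.

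Pooling carries a risk of its own. If the effect exists at one site only, pooled power at 0.478 falls to 26%.

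Finally, centre handling is often left to a fuller plan. Here, however, the article lists the factors, covariates and random effects of both models, and Site is not among them.

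**Conclusion.** The point holds for 2-back accuracy and reaction time, 2-back dual-task cost and the shared secondary tests. Gait, posturography, CRM and fNIRS outcomes exist at one site only and are unaffected.

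The plan leaves open whether a shared outcome gets one test or two. Two tests carry a 9.75% chance of at least one false success per outcome, whatever the effect size. The power cost of splitting is material for moderate effects (45% against 74% at 0.478) and modest for large ones (89% against 99.5% at 0.83), on the assumption that the cited effects are between-arm differences in change. The cost of pooling without Site is 6% to 25% more change variance under the assumed 0.5 to 1 SD difference in retest change, and nothing for a difference in level.

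This is a gap in specification that should be closed, and it does not invalidate the design. The any-outcome success rule across different primary measures is a separate multiplicity question and is not counted here.

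**What to change.** For outcomes measured comparably at both sites (2-back accuracy and reaction time, and the shared secondary tests), name one deciding test: Time x Training Group over all 120 participants, with Site and Site x Time added to the ANOVA and the mixed model. Report Site x Time x Training Group and the site-specific estimates with confidence intervals as descriptive.

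Report the 2-back dual-task cost by site, because its companion motor task differs, and treat any pooled estimate as supportive. Keep gait, posturography and CRM as single-site analyses.

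The cost is analysis wording and two model terms, with no new data. The article says recruitment is still ongoing, so the choice can be fixed before results are known. The small downside is that pooled dual-task 2-back accuracy and reaction time average over two settings that differ in trial length, posture and audibility calibration. The site-specific estimates make that visible, and they would also show an effect confined to one site.

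### The primary test does not adjust for the baseline outcome, and the second model has no stated precedence and omits Time × Training Group from its listed terms

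*Protocol article*

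**What the plan says.** All of this stands in the protocol article under Planned analyses, unless another section is named.

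- **Primary model.** "separate 3 × 2 × 2 Mixed Factorial ANOVAs will be conducted for each of the primary outcome measures". The between-subjects factors are age/hearing group and training group, and the within-subject factor is time (pre, post). On covariates: "Covariates will include sex and education". The baseline value of the outcome enters as one of the two repeated measures, not as a covariate.
- **Primary test.** "Observation of a statistically significant Time by Training Group interaction in any of the primary outcome measures" counts as preliminary evidence of efficacy.
- **Second model.** "Linear mixed effects models will also be fitted for each of our outcome measures, particularly if there is a large amount of missing data". Unequal variances across groups are the other condition named. No threshold is given for either condition, and neither model is said to take precedence.
- **Terms of the second model.** Age/hearing group, then "Training Group (executive function training, control), Sex (male/female), and Time (Pre- vs. Post-Training), Random effects will include the individual participants", with education as covariate. No interaction is listed.
- **Timing of baseline.** Study procedure and Randomization both place the baseline assessments before randomisation.

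**The concern.** A baseline value measured before randomisation can be used as a covariate without bias. With two time points, leaving it out makes the Time × Training Group test a comparison of raw change. That gives away precision in a trial with about 30 participants per arm at each site.

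The second model raises two further questions. The plan does not say which result counts if the two models disagree. And a mixed model contains only the terms written into it: without Time × Training Group, no term in it corresponds to the primary hypothesis. This is also the model that the plan would lean on when data are missing.

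**Working it through.** **Inputs.** From Sample size: power 0.95 and alpha 0.05 ("The recommended (G*Power) sample size to achieve a power of 0.95 at an alpha level of 0.05"), 18 per group, 10% attrition, and effect sizes 0.304 (Time × Training Group) and 0.478 (Time, trained group), both labelled d. From Planned analyses: "All statistical tests will be two-tailed". From Design and Randomization: 60 per site in two equal arms, so 30 per arm and 30 × 0.9 = 27 completers. Pre-post correlation ρ: not given, so assumed, with a range of 0.3 to 0.9.

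**1. The plan's own figure.** For a within-between interaction with two groups and two times, λ = f² × N × 2/(1−ρ), with 1 and N−2 degrees of freedom. Entering 0.304 as Cohen's f with ρ = 0.5 gives 19 per group. At 18 per group the power is 0.943. The stated 18 is therefore reproduced within rounding, and 18/0.9 = 20. It is not reproduced if 0.304 is d as labelled: f = 0.304/2 = 0.152 gives 72 per group. That is a separate matter, but it affects how much the precision is worth.

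**2. Precision of the two estimators.** With common variance σ² at both times:

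- change: 2σ²(1−ρ)
- baseline-adjusted: σ²(1−ρ²)
- ratio: (1−ρ²)/(2(1−ρ)) = (1+ρ)/2

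| ρ | Variance ratio | Reduction in standard error |
|---|---|---|
| 0.3 | 0.65 | 19% |
| 0.5 | 0.75 | 13% |
| 0.7 | 0.85 | 8% |
| 0.9 | 0.95 | 2.5% |

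The gain depends on equal variances. If the baseline SD is k times the post SD, the ratio is (1−ρ²)/(k²+1−2ρk). At ρ = 0.6:

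- k = 1: 0.64/0.80 = 0.80
- k = 0.8: 0.64/0.68 = 0.94
- k = 0.6: 0.64/0.64 = 1.00, so no gain

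**3. Effect on power**, at ρ = 0.5, dividing λ by (1+ρ)/2 and giving up one degree of freedom:

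| Effect size read as | n per arm for 0.95: change | n per arm: adjusted | Power at 27 per arm: change | Power: adjusted |
|---|---|---|---|---|
| 0.304 as f | 19 | 15 | 0.992 | 0.999 |
| 0.478 as d (f = 0.239) | 30 | 23 | 0.931 | 0.978 |
| 0.304 as d (f = 0.152) | 72 | 54 | 0.592 | 0.716 |

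**4. Simulation.** 4,000 runs, 27 per arm, true effect 0.50 outcome SD (an assumed value on its own scale, not comparable with the table above):

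| ρ | Mean estimate: change / adjusted | Empirical SD | Power |
|---|---|---|---|
| 0.5 | 0.50 / 0.50 | 0.274 / 0.241 | 0.44 / 0.54 |
| 0.7 | 0.50 / 0.50 | 0.213 / 0.197 | 0.65 / 0.71 |

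Both methods estimate the same effect; only the spread differs.

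**5. The mixed model as listed.** With main effects only and complete data, the Training Group coefficient is the average of the pre and post differences between arms. Randomisation makes the expected pre difference zero, so for a true effect δ the coefficient is (0+δ)/2 = δ/2. In the same simulation it averaged 0.25 against a true 0.50.

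**The case against.** The planned primary test is valid, and several stronger readings go too far.

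- **A reader might call the test unadjusted.** It is adjusted for sex and education; only the baseline outcome is left out.
- **A reader might infer a data-driven switch of model.** The article says that mixed models are fitted in addition, and it names the ANOVA as the evaluation of the primary hypothesis. With complete data, a random-intercept model that includes Time × Training Group gives essentially the same test as the ANOVA. No inflation of the error rate has been shown here. What stands is that precedence is not stated and that the conditions have no threshold.
- **A reader might infer that the ANOVA estimates the wrong effect.** It does not: its interaction is unbiased for the training effect.
- **A reader might infer that the plan cannot test its primary hypothesis.** The ANOVA can. The ANOVA sentence also lists only factors, and the interaction is named in the next sentence, so the missing term in the mixed model may be condensed wording. Still, a factorial ANOVA contains its interactions by construction and a mixed model does not, so the term should be written out.
- **Missing post values.** Dropping participants without one is not peculiar to the ANOVA, since a complete-case ANCOVA drops the same people. The article also says that data will be corrected for missing values.

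The size of the gain is open too. It is slight if ρ is high, and it vanishes for some unequal variances. On the reading that reproduces 18 per group, power at 27 per arm is already 0.992.

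**Conclusion.** The point holds as a gain in precision and a needed clarification, not as a bias. Under equal pre and post variances, baseline adjustment reduces the variance of the training effect by 35% at ρ = 0.3, 25% at 0.5, 15% at 0.7 and 5% at 0.9. In large samples it is never less precise than the change comparison. Its practical value runs from negligible (0.304 as f) to material (0.304 as d: power 0.59 to 0.72 at 27 per arm, ρ = 0.5). The article gives neither ρ nor the two variances, so the gain cannot be fixed more closely.

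The second model has no stated precedence. Read literally, its Training Group term estimates about half the effect and does not test the primary hypothesis. That last conclusion rests on taking the listed terms as complete.

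**What to change.** Name one governing model for each primary outcome: a linear mixed model on all randomised participants, with a baseline mean constrained to be common to the two training arms, Time × Training Group listed explicitly, and age/hearing group, sex and education. The complete-case counterpart is an ANCOVA of the post value on training, baseline, age/hearing group, sex and education.

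Take the overall training effect from a model without the training × age/hearing product, or as the average over the age/hearing groups. Otherwise, under reference coding, the training coefficient is the effect in one subgroup only.

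Delete the condition that ties use of the mixed model to missing data or unequal variance, and keep the mixed ANOVA as a sensitivity analysis.

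The cost is analysis wording and one degree of freedom. The baseline measurements are already planned, so no new data are needed.
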